### Study Procedures

#### Facility-Level Eligibility, Recruitment, and Data Collection

We have enrolled all 4 Wits RHI TG-DSD sites listed in Table 2. In collaboration with district health departments, we have recruited 1 SSD site within the catchment area of each DSD site for a total of 4 TG-DSD sites and 4 SSD sites. SSD sites are similar to TG-DSD sites in urbanicity, socioeconomic status of the client population, and types of HIV services offered (ie, both ART and PrEP). We shared information about the study with the district and SSD site leadership and invited them to participate in the study. Study staff will visit all 8 recruited sites (TG-DSD and SSD) to complete a standardized observation checklist at baseline and 12 months. Checklist items include the number, type, and role of staff; content and frequency of staff training; facility hours, amenities (eg, number of rooms), and community outreach efforts; standard policies and procedures for delivery of HIV and sexually transmitted infection testing, PrEP, ART, and GAHT services, including, but not limited to counseling, prescribing, dispensing, laboratory monitoring, tracking, and visit frequency; sex and gender documentation on clinical forms and records; the number of transgender clients; number of transgender people prescribed GAHT; number of transgender people prescribed PrEP; number of transgender people prescribed ART; availability and use of psychosocial services; and cost of service delivery.

Leadership at each recruited site facilitate recruitment of 6 staff members per site (n=48) to complete a KII at baseline and 12 months. Eligible staff members are aged ≥18 years and work for 1 of the TG-DSD sites or a selected SSD site. We enroll 1 person in each role at each site, that is, peer navigator, community liaison officer, social worker, community health worker, nurse, and site manager. If a staff member leaves between baseline and 12 months, we will interview another person in the same role for the 12-month time point. We contact potential key informants via email or WhatsApp and invite them to participate.

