An experienced qualitative researcher conducts the KIIs after the informed consent process. A semistructured KII guide will be used to organize the interview. KIIs last approximately 60 minutes and include open-ended questions that explore facilitators, barriers, strengths, and weaknesses of the DSD and SSD approaches and recommendations for improving service delivery. At the end of the qualitative interview, participants complete a brief, interviewer-administered quantitative tool measuring antitransgender stigma [71] and validated measures of intervention acceptability, feasibility, and appropriateness [72,73]. KIIs are audio-recorded with permission of the participant, and notes are taken during and after the interview to facilitate accuracy and appropriate analysis. Where possible, interviewers are fluent in local languages. When interpretation is required, a trained study staff member interprets during the interview.

We collect data on the costs of implementation at all TG-DSD sites by conducting a bottom-up analysis of the resources used and costs accrued by all transgender cohort participants who receive TG-DSD. We also collect facility-level data on overhead cost items, such as space, administration, and utility costs, and allocate these to the service and our cohort based on the number of visits. We use our extensive database of public sector prices and salaries, as well as information on staff levels at each site, to estimate the public sector costs; these are data we have used in other costing studies in South Africa [53,74,75].

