Sample sizes for qualitative inquiries are designed to collect enough data to reach theoretical saturation, defined as the point at which no new themes emerge from ongoing data collection [95]. Samples sizes as low as 6 can achieve saturation when the study population is homogeneous. However, a sample size of 12 to 20 is typically needed, fewer for longitudinal studies. To account for diversity by site, role, gender identity, education level, etc, we have chosen a sample size of 48 individuals for KII participants, for a total data set of 96 KIIs (including baseline and 12 months). We have selected a smaller sample size of 15 per arm (n=30) for IDIs with transgender clients as they will share similarities which will produce a robust data set of 60 total IDIs for analysis.

### Quantitative Data Analysis for Aim 1

Standardized checklists from DSD and SSD sites will be examined using descriptive statistics. We will perform chi-square tests or Fisher exact tests for associations between categorical variables. We will perform unpaired Student *t* tests to compare continuous variables or outcomes between 2 groups. We will perform Wilcoxon rank sum tests, if data are not normally distributed.

In the DSD sites, to assess acceptability and perceived feasibility of implementing the differentiated care model, staff at each implementing site will complete a brief survey with implementation outcome measures at 12 months. The Acceptability of Intervention Measure (AIM), the Intervention Appropriateness Measure (IAM), and the Feasibility of Intervention Measure (FIM) will be used to quantitatively measure implementation outcomes related to the TG-DSD model [73]. Each measure consists of 4 items, with response options on a Likert scale from 1 (completely disagree) to 5 (completely agree), for a possible summary score range from 4 to 20. Higher scores indicate greater acceptability and feasibility.

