Descriptive statistics will be used to characterize each measure overall and by site. On the basis of a score of 4 (agree) for all 4 items in the scale, a summary score ≥16 on each scale would be consistent with overall agreement that the strategy was acceptable or feasible, respectively [73]. Therefore, we will test the hypothesis that the overall mean score for each measure (AIM and FIM) is ≥16 using a 1-sample *t* test. If score data deviate from normality (skewed or nonnormal), we will conduct a 1-sample Wilcoxon signed test. We will conduct a secondary analysis to test for significant changes in baseline and 12-month scores across sites using paired sample *t* tests for normally distributed data or Wilcoxon signed rank tests if the data are nonnormal.

Using data from both study arms, facility-based stigma will be measured using the brief health facility stigma tool [71]. Each item includes 4 response options on a Likert scale that ranges from “never” to “most of the time.” Higher scores indicate greater facility-based stigma. Descriptive statistics will be generated as outlined earlier for the implementation outcome measures. We will compare mean summary scores at TG-DSD sites versus SSD sites at baseline and at 12 months, using 2-sample *t* tests if normally distributed or Wilcoxon rank tests if nonnormal. Exploratory analyses will include Pearson correlation analyses and bivariate regression to assess associations between site characteristics (eg, location and urbanicity), including facility-based stigma scores and the aforementioned implementation outcome scores.

### Qualitative and Quantitative Data Integration for Aim 1

Qualitative and quantitative data will be integrated using results-based convergent synthesis in which they will be analyzed separately then merged using joint display [96-98]. Qualitative themes will triangulate and provide context for facility stigma scores and implementation measures. Data from the checklists will be integrated into the joint display to assess visually any relationships between site features and the relationship between TG-DSD and HIV outcomes. Integrated displays will be used to identify implementation patterns. The qualitative code density (frequency of each code) will be displayed by service delivery model (TG-DSD vs SSD). Visualization will facilitate identification of similarities and differences in participant experiences across models.

### Data Analysis for Aim 2

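### Aim 1 tests on staff stigma and implementation scores ignore clustering within 8 sites, and the paired test of implementation scores does not fit the rule that replaces staff who leave

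*Protocol article*

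**What the plan says.** **Who is measured.** The design has one TG-DSD and one SSD site in each of 4 areas, "for a total of 4 TG-DSD sites and 4 SSD sites". Site leadership helps with "recruitment of 6 staff members per site (n=48) to complete a KII at baseline and 12 months" (Facility-Level Eligibility, Recruitment, and Data Collection). At the end of each interview, "participants complete a brief, interviewer-administered quantitative tool measuring antitransgender stigma", together with the acceptability, feasibility and appropriateness scales. The sample size paragraph counts 48 informants, "for a total data set of 96 KIIs (including baseline and 12 months").

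**How the scores are tested** (Quantitative Data Analysis for Aim 1).
- Stigma: "We will compare mean summary scores at TG-DSD sites versus SSD sites at baseline and at 12 months", by 2-sample t test, or a Wilcoxon rank test if scores are not normal. The two time points are tested separately.
- AIM and FIM: the overall mean is tested against 16 by a 1-sample t test or its Wilcoxon counterpart.
- Change in implementation scores: a secondary analysis will "test for significant changes in baseline and 12-month scores across sites using paired sample" t tests, or signed rank tests.

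**Who is measured the second time.** "If a staff member leaves between baseline and 12 months, we will interview another person in the same role for the 12-month time point".

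**Clustering.** The client-level Aim 2 models have random site intercepts and a general commitment to account for clustering (Data Analysis for Aim 2). No such statement accompanies the Aim 1 staff tests.

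**The concern.** Service model is a property of the site. Six colleagues share management, training and working culture, so they are not six independent observations of what a service model does. A test on 24 versus 24 staff takes its precision from 48 people, whereas the comparison rests on 4 versus 4 sites. The 1-sample tests on TG-DSD staff share the problem, with only 4 sites behind them.

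The article itself gives reason to expect site differences. Table 2 shows sites differing in model, urbanicity and where hormone therapy is provided, and Aim 1 plans to relate site characteristics to these same scores.

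The paired analysis raises a different question. Where a post changes hands, the baseline and 12-month scores belong to two people. Pairing them presents a change of personnel as a change of opinion; dropping them restricts the result to those who stayed. The article does not say which is meant.

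Acceptability and feasibility are the substance of Aim 1, and the facility stigma scale is among the mediators named for Hypothesis 3. A falsely significant staff result would be read as supporting the expected mechanism.

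**Working it through.** **Counts.** 8 sites × 6 staff = 48; × 2 time points = 96 interviews. This reproduces the article's figures. Each arm has 4 × 6 = 24 staff. The article states no power for these tests and no ICC, so the ICC below is an assumption, shown over a range.

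**Design effect.** DEFF = 1 + (m − 1) × ICC with m = 6; effective staff per arm = 24 / DEFF. At ICC .20: DEFF = 1 + 5 × .20 = 2.0, effective number 12, and the standard error is understated by √2.0 = 1.41. A hand check: the critical value 2.01 (46 df) then acts like 2.01 / 1.41 ≈ 1.42, a two-sided normal tail of about 16%.

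**Simulation of the planned tests.** Normal scores, no true difference, two-sided nominal 5%, 40,000 runs (8,000 for Wilcoxon).

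| Assumed ICC | DEFF | Effective n per arm | 2-sample t | Wilcoxon | 1-sample t |
|---|---|---|---|---|---|
| .01 | 1.05 | 22.9 | 5.3% | 4.9% | 5.5% |
| .05 | 1.25 | 19.2 | 8.2% | 7.6% | 7.8% |
| .10 | 1.50 | 16.0 | 10.8% | 10.2% | 10.8% |
| .20 | 2.00 | 12.0 | 16.7% | 15.9% | 16.6% |
| .30 | 2.50 | 9.6 | 22.6% | 21.5% | 22.3% |

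A t test on the 8 site means (6 df) stays at 4.8% to 5.1% throughout. A 1-sample test on the 4 TG-DSD site means (3 df) stays at 4.9% to 5.3%.

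**Area matching.** Variance shared by both sites of an area cancels in the arm difference. For the 2-sample t test at ICC .05/.10/.20/.30:
- half the site variance shared: 6.3/7.6/10.4/13.6%;
- all of it shared: 4.6/4.2/3.6/2.8%, which is conservative.

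**Role balance.** One person per role is interviewed at each site, so role differences add to the residual variance but not to the arm difference. For the 2-sample t test at ICC .01/.05/.10/.20/.30:
- assumed role share of variance 20%: 3.8/6.0/9.3/15.6/21.6%;
- assumed role share 40%: 2.3/4.7/7.8/14.3/20.9%.

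**Paired test of change.** 24 TG-DSD staff, assumed person variance share .5 and site ICC .10, with 0/25/50/100% of staff replaced:
- no site-by-time variance: type I error 4.8% to 5.0%; power for a 0.6 SD change 88/78/70/56%;
- site-by-time variance share .05: type I error 12.4/10.6/9.7/8.2%.

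A constant site effect cancels in the difference, so replacement alone does not inflate the error. Inflation here needs sites that change differently over time.

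**Timing.** Quantitative Data Analysis for Aim 1 first places the staff implementation survey at 12 months, then tests change from baseline. The data collection section attaches the scales to interviews held at both times. Without baseline scores the paired test cannot be run.

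**The case against.** The strongest reply is that the inflation rests wholly on an ICC the article does not give. At .01 the 2-sample test runs at 5.3%, which is harmless. Area matching and role balance pull the figure down further and can remove or reverse the inflation at low ICCs. This stands, and it is why the size must be stated as conditional. It does not remove the concern: with half the site variance shared, or with a 20% role share, the 2-sample test still exceeds 5% at every ICC from .05 up. Matching cannot help the 1-sample tests, which have no comparison arm.

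A second reply is that these are supporting analyses. The three formal hypotheses belong to Aim 2, mediation is tested by structural equation modeling, the paired test is labelled secondary, and staff scores are also described by site and set beside qualitative themes. This stands too, and it limits what is at stake.

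Third, the reference to change across sites could mean pairing site scores, which would create no false pairs of people, and a full protocol may say how replacements are handled. The text allows that reading but does not state it.

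A reader might also infer that the stigma comparison is spoiled by false pairs, or that false pairs make p values too small. Neither is supported. Stigma is compared by separate 2-sample tests at each time point, with no pairing, and false pairs by themselves left the error at about 5% in the check above.

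**Conclusion.** The concern holds in two separate parts.

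1. The stigma comparison and the AIM and FIM tests against 16 treat staff within a site as independent. At assumed ICCs of .05 to .30, a nominal 5% is about 8% to 23% for the 2-sample t test and 8% to 22% for the 1-sample test. The 2-sample figure falls to about 6% to 14% if half the site variance is shared within areas. There is no inflation if all of it is shared or the ICC is near zero. It would therefore go too far to say that these p values are known to be too small.
2. For implementation scores only, the paired test does not fit the replacement rule. The harm is lost power and a change estimate that mixes turnover with real change. How large it is depends on staff turnover, which the article does not give.

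Both are worth correcting because the change is cheap. The primary viral suppression analysis is untouched.

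**What to change.** - **Stigma:** compare the 8 site means with a t test on 6 df, or analyse the 4 within-area differences (3 df), which uses the matching. Alternatively, fit a linear mixed model with a random site intercept and small-sample degrees of freedom.
- **AIM and FIM against 16:** test the 4 TG-DSD site means (3 df) or use an equivalent site-level model. With so few sites, reporting them descriptively with intervals that allow for clustering is also defensible.
- **Change in implementation scores:** use a mixed model with time as a fixed effect and person and site effects, so that stayers contribute paired information and replacements unpaired information. Otherwise restrict the paired test to staff interviewed at both times, and say so. With 4 sites, a site variance is poorly estimated, so results should be worded cautiously.
- **Timing:** reconcile the two statements on whether AIM, IAM and FIM are collected at baseline.

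If both interviews carry the scales, this is analysis wording only and needs no new data. The cost is wider intervals and less apparent power: the critical value rises from 2.01 (46 df) to 2.45 (6 df), or to 3.18 with 3 df. That is the real precision of 8, or 4, sites.

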## Methods

### Overall Study Design

Jabula Uzibone is an observational, multisite, mixed methods, and prospective implementation study. To meet the first aim, we will assess the implementation of TG-DSD models and SSD models at the facility level using standardized observation checklists at 8 facilities (1 DSD site and 1 SSD site per area in all 4 areas). We will examine implementation, acceptability, feasibility, and barriers to and facilitators of TG-DSD via key informant interviews (KIIs; n=6 per site) with health facility staff. At the client level, we will conduct in-depth interviews (IDIs) with 30 transgender people (15, 50% from DSD sites and 15, 50% from SSD sites) drawn from the longitudinal cohort enrolled for aim 2 described in the next paragraph.

To meet the second aim, we will enroll a cohort of ≥600 transgender people and follow them for 12 months. Of the transgender people enrolled, ≥400 (66.7%) will be transgender people living with HIV. This will include ≥200 (50%) who receive ART at TG-DSD sites and ≥200 (50%) who receive ART at SSD sites in the same area as the TG-DSD sites. We will also enroll ≥200 transgender people without HIV. This will include ≥100 (50%) participants without HIV at TG-DSD sites and ≥100 (50%) without HIV at SSD sites in the same area as the TG-DSD sites. Each participant will complete a quarterly survey to assess engagement in HIV prevention and care, changes over time in experiences of gender affirmation, and experiences of stigma.

For participants on ART, we will measure HIV RNA levels (ie, viral load) at baseline and 12 months. For participants on PrEP, we will measure tenofovir levels at baseline and 12 months. For participants who are HIV negative and not on PrEP, we will assess self-reported condomless sex. Prevention-effective adherence is defined as being HIV negative and meeting one of the following criteria: (1) adherent to PrEP based on tenofovir levels, (2) self-report of consistent condom use in the prior 30 days, or (3) self-report of no anal or vaginal sex in the prior 30 days. Table 1 presents a list of data collection activities organized by level of analysis, participant type, and month of enrollment.

**Table 1 table1:** Data collection activities by level of analysis, participant type, and month of enrollment.

Level			Participant, n (%)		Baseline		Months 3, 6, and 9		Month 12

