We will use quantitative methods to evaluate the effectiveness of TG-DSD for viral suppression and prevention-effective adherence and to assess stigma and GAHT use as potential mediators. As noted earlier, our first hypothesis is that rates of viral suppression are more likely to increase among transgender people on ART at TG-DSD sites than among transgender people on ART at SSD sites over the 12-month study period.

The primary outcome measure is the proportion of transgender people on ART with viral suppression (HIV RNA <50 copies/mL). Descriptive analyses will summarize HIV viral suppression comparing participants at TG-DSD versus SSD sites as well as by gender identity at baseline and 12 months. Percent distributions will be computed for categorical variables and means, ranges, SDs, medians, and IQRs will be presented for continuous variables stratified by attendance at TG-DSD versus SSD sites. The primary estimate for this aim is the absolute difference in the change in proportion of virally suppressed during the study period between participants at TG-DSD sites and those at SSD sites. A difference-in-difference (D-i-D) analysis will be conducted to account for anticipated differences between groups at baseline (TG-DSD vs SSD). In addition, we will compare differences at 12 months considering baseline values to enhance the robustness of the estimators of the differences in the 2 groups.

A mixed-effects binomial model will be fit, where the binary viral load suppression status of each client is regressed on fixed effects for time (baseline vs 12 months), TG-DSD versus SSD site, the time by site model interaction, and client-level covariates (age and gender identity). In addition, random intercepts for each of the sites will be included in the model to account for within-site correlation. The D-i-D estimator is the estimated regression coefficient for the time by service delivery model interaction term. All models will account for clustering and be adjusted for relevant confounders in baseline covariates.

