**Figure 1 figure1:**
[figure not shown]
Structural equation model to test stigma and gender affirmation as mediators of relationships between service delivery type and HIV outcomes.

### Exploratory Analyses for Aims 1 and 2

We will conduct 3 exploratory analyses. First, using longitudinal data from baseline, 3, 6, 9 and 12 months, we will perform mixed-effects regression modeling to analyze changes in stigma scores, psychological gender affirmation scores, and GAHT use over time by service delivery model. Mixed-effects regression is most appropriate for clustered longitudinal data as it captures correlations of repeated measures using random effects that describe cluster-specific trends over time [100]. Second, as sample size allows, we will assess HIV outcomes by subgroups. The D-i-D model, used to test hypothesis 1 and hypothesis 2, will be fit separately for subgroups defined by (a) gender identity, (b) sex assigned at birth, (c) individual care facility, and (d) colocated versus stand-alone TG-DSD sites. Third, the association between 12-month HIV outcomes (viral suppression rates and prevention-effective adherence rates) and implementation metrics from aim 1 will be examined graphically for the 4 TG-DSD sites by plotting the HIV outcomes at each site versus mean scores on the AIM, IAM, and FIM, respectively.

The use of D-i-D analyses implicitly assumes that TG-DSD sites are either comparable with SSD sites (other than the DSD approach) or that we can readily adjust for any differences. However, if we find that groups differ on important characteristics, we will use inverse probability of treatment weighting to adjust for the covariates in the effect estimation to mitigate potential bias.

### Data Analysis for Aim 3

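### The primary model names random intercepts for sites only, so as written it ignores the correlation between a client's baseline and month-12 results and misstates the D-i-D standard error, most likely on the conservative side

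*Protocol article*

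**What the plan says.** Data Analysis for Aim 2 sets out the primary model term by term. It is a mixed-effects binomial model with fixed effects for time, service model and their interaction, plus age and gender identity. The random part is given in one sentence: "random intercepts for each of the sites will be included in the model to account for within-site correlation". The estimator is then fixed: "The D-i-D estimator is the estimated regression coefficient for the time by service delivery model interaction term". A general sentence closes the paragraph: "All models will account for clustering and be adjusted for relevant confounders in baseline covariates".

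The same section names the absolute difference in the change in proportion suppressed as the primary estimate. It carries the same steps over to prevention-effective adherence (hypothesis 2).

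Overall Study Design shows that the data are paired: "For participants on ART, we will measure HIV RNA levels (ie, viral load) at baseline and 12 months".

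Exploratory Analyses for Aims 1 and 2 justifies mixed-effects regression for the quarterly stigma, gender affirmation and GAHT data on the ground that "it captures correlations of repeated measures using random effects that describe cluster-specific trends over time". No such provision is stated for the primary model.

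**The concern.** The time-by-model interaction compares changes within the same people. Given a site intercept and covariates, a model without a client term handles two results from one client exactly like results from two different clients at that site. The variance of a change is then taken as the sum of two variances, and the covariance that should be subtracted is left out.

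Suppression at baseline and at 12 months is likely to be positively correlated within a client. If so, intervals are too wide and the test rejects too rarely. Part of the precision gained by following a cohort is lost. A null result could then owe something to the variance formula and yet be read as evidence against TG-DSD.

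**Working it through.** **Inputs from the documents.** Planning rates (Statistical Power): TG-DSD 65% to 85%, SSD 61% to 66%, so the D-i-D is 0.20 − 0.05 = 0.15. Minimum of 172 per group, two-sided α = 0.05, power 0.80, loss about 12%. There are eight sites: "for a total of 4 TG-DSD sites and 4 SSD sites".

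**Assumption.** The within-client correlation ρ is not given; I use 0.2 to 0.5. The planning rates cap it in the TG-DSD arm at (0.65 × 0.15)/√(0.2275 × 0.1275) = 0.57, so the range is attainable.

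**The plan's own figure.** The article does not state which p₁ it used. Taking the 47% it cites, against 62%, with the pooled two-sided formula:

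n = [1.96·√(2 × 0.545 × 0.455) + 0.8416·√(0.2491 + 0.2356)]² / 0.15² = (1.380 + 0.586)² / 0.0225 = 171.8, so 172.

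Then 172/0.88 = 195.5, so 196, rounded up to 200. The figure reproduces, but as a comparison of two proportions at one time point. It uses neither the pairing nor the D-i-D variance, so it does not settle the present question.

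**Risk-difference scale.** With v = p(1−p), the four variances are 0.2275, 0.1275, 0.2379 and 0.2244, which sum to 0.8173. The within-arm products are √(0.2275 × 0.1275) = 0.1703 and √(0.2379 × 0.2244) = 0.2311, which sum to 0.4014.

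Var(D-i-D) = [0.8173 − 2ρ × 0.4014]/172

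The model as written sets ρ = 0, so SE₀ = √(0.8173/172) = 0.0689.

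**Logit scale (delta method).** The D-i-D in log-odds is 1.116 − 0.216 = 0.900. The reciprocals 1/v sum to 20.90 and the cross terms to 10.20.

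Var = [20.90 − 2ρ × 10.20]/172, with SE₀ = 0.349.

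**On either scale**, with δ the D-i-D and SE the value at the true ρ:
- true size = 2[1 − Φ(1.96·SE₀/SE)]
- power as written = Φ((δ − 1.96·SE₀)/SE)
- power with pairing = Φ(δ/SE − 1.96)

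| ρ (assumed) | True SE, risk difference | SE₀ too large by | True size of 5% test | Power, risk difference: as written / paired | Power, logit: as written / paired |
|---|---|---|---|---|---|
| 0.2 | 0.0618 | 12% | 2.9% | 60% / 68% | 76% / 82% |
| 0.3 | 0.0579 | 19% | 2.0% | 60% / 74% | 77% / 87% |
| 0.4 | 0.0537 | 28% | 1.2% | 61% / 80% | 79% / 91% |
| 0.5 | 0.0492 | 40% | 0.6% | 62% / 86% | 81% / 95% |

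The SE excess and true size shown are for the risk difference; on the logit scale they are nearly the same.

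**Simulation check.** Eight sites of 44 clients were simulated with a binary correlation of about 0.4. A logistic model was fitted with fixed site effects standing in for the random site intercept. With no effect, the empirical SE was 0.264, the model-based SE 0.330 and the client-clustered SE 0.260. Rejection was 1.2% with the model-based SE and 5.5% with the client-clustered SE. Under the planning rates, power was 0.80 and 0.92. This agrees with the ρ = 0.4 row.

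**The case against.** The strongest reply is the sentence "All models will account for clustering and be adjusted for relevant confounders in baseline covariates". It could cover clients as well as sites, the exploratory section shows that the team knows how to handle repeated measures, and an analysis plan not shown may specify a client term or client-clustered errors. That possibility stands, and a reader should not infer that the authors intend to treat clients as independent; the article does not say so. But the sentence names no client unit, and it follows a model whose only stated cluster is the site. The article does not leave the random effects open; it fixes them, and incompletely.

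Four stronger readings are tempting, and the documents do not support them.

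- **False positives.** With positive correlation this omission makes the test conservative.
- **A certain direction of error.** The model also has no site-by-time random effect. With eight sites, differing site trends could make the reported SE too small, so the net direction is not known.
- **Power of about 60% under the specified model.** That figure belongs to the risk-difference scale. The article specifies a binomial model without naming the link, and on the logit scale power as written stays near the planned 80%.
- **Broken handling of missing data.** Overall Approach to Data Analysis provides for multiple imputation when more than 10% is missing, and the expected loss of about 12% exceeds that. It also plans sensitivity analyses for departures from missing at random. Data Analysis for Aim 2 adds a 12-month comparison that takes baseline into account. These largely answer the point about dropouts, though they do not correct the D-i-D standard error.

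**Conclusion.** The point holds as a should-fix matter. As written, the primary model for hypothesis 1, carried over to hypothesis 2, omits the within-client correlation, so its model-based D-i-D standard error is wrong unless that correlation is zero.

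The sizes in the table rest on three assumptions: a correlation of 0.2 to 0.5 that the documents do not give, the article's own planning rates with 172 per arm, and time trends shared by the sites under each service model. They were worked out for viral suppression only; the defect carries over to prevention-effective adherence, but its size there was not computed. The likely consequence is lost precision and power, not a spurious finding.

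**What to change.** State how within-client correlation enters the primary models for hypotheses 1 and 2, and name one approach as primary:

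- **Client random intercept nested within site.** Under a logit link the interaction coefficient becomes client-specific, so the absolute D-i-D that the article names as its primary estimate should come from marginal (population-averaged) predictions.
- **Marginal model** whose variance accounts for repeated measures within client. If variance is clustered on the eight sites instead, add a small-sample correction.

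The two are not equivalent: they target different coefficients, and they differ in what they require of missing data. Site-specific time trends should be considered at the same time, since they may act on the standard error in the opposite direction.

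The cost is a revised model statement and, for the first option, the extra step of marginal standardisation. No further data are needed.
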